### Adverse events

2.12

In this study, all adverse events occurring during the clinical trial will be examined and recorded. The adverse event refers to any undesirable and unintended signs (e.g., abnormalities in the laboratory test results), symptoms, or diseases that appear after the treatment in the clinical trial process, and is not necessary that the adverse event has a causal relationship with the treatment. Adverse events will be collected through patient complaints or observations, and the occurrence of adverse events between groups will be examined by occurrence frequency.

The investigator will evaluate the causal relationship between the respective treatment method and the adverse events that occurred on a 6-point scale (1 = definitely related, 2 = probably related, 3 = possibly related, 4 = probably not related, 5 = definitely not related, and 6 = unknown). In addition, the severity will be categorized into 3 levels using Spilker classification method.

1.Mild did not impair the participant's normal activities of daily living (ADLs), caused minimal discomfort and required no additional treatment2.Moderate: significantly impaired the participant's normal ADLs and may have required treatment but they were resolved after treatment, and3.Severe: severely impaired the participant's normal ADLs, required intense treatment, and left sequelae)

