## Introduction

1

Neck pain is one of the common musculoskeletal disorders in the general population. Although the prevalence of neck pain varies by studies conducted and the time period, the 1-year prevalence rate is reportedly 25.8%^[1]^ and the prevalence in an adult's lifetime is 50%.^[2]^ Neck pain can develop into considerably severe pain, disability, and cause a financial burden.^[3]^ Years lived with disability from neck pain per 100,000 population was reportedly 352 from 1990 to 2017,^[4]^ and the neck pain was the fourth main cause of years lived with disability according to the 2016 Global Burden of Disease.^[5]^

Among the different types of neck pains, acute neck pain is considered a self-limiting disorder and adults can experience pain during typical activities (e.g., lifting, twisting, and stretching). Acute neck pain is caused by loads applied internally to the tissues or external loads such as a fall and direct impact to the head or neck. However, little is known about the prevalence and treatment of acute neck pain, especially those not caused by whiplash. Vernon et al^[6]^ reported that the point prevalence of acute neck pain to be around 10%. There is currently no consensus for the definition of acute neck pain but is often defined as pain that does not last for more than 4 weeks.^[7,8]^ There is no standardized guideline for the treatment of acute neck pain but in a study of patients that visited general practitioners for acute neck pain in the Netherlands, 42% of patients were prescribed non-steroidal anti-inflammatory drugs and muscle relaxation.^[9]^ In addition, other studies have reported on the effectiveness of laser therapy^[10]^ and cervical spine thrust manipulation^[11]^ on acute neck pain.

The motion-style acupuncture technique (MSAT), which combines traditional acupuncture and movement therapy, is a treatment that induces passive and active movements of the patient with the needles inserted, after a traditional acupuncture treatment. All movements are made under the observation and guidance of a physician. MSAT has been increasingly used to relieve musculoskeletal pain in Korean clinical practice and recently has gained attraction in China as a method to enhance the effect of traditional acupuncture treatment.^[12–14]^ However, the supporting evidence and data for the effectiveness and safety of MSAT are insufficient as only a few related studies have been conducted.

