#### Experimental group: MSAT

2.3.1

The protocol for trapezius MSAT is as follows; the patient sits on a chair or the floor, straightens from low back up to the neck, pulls their chin slightly toward the body, and directs their gaze towards the front. In this position, the physician rotates the neck alternately from left to right with 3 disposable needles (30 mm ∗ 0.25 mm; Dong-bang Acupuncture, Korea) inserted into the upper trapezius on both sides of the subject at a depth of about 5 to 10 mm. The neck movement range shall only be up to the ROM and the physician examines whether there is a difference from the normal ROM and presence of other abnormalities in the movement. When the side with the smaller left-to-right ROM is set as the affected side, the left-to-right turning motion is performed regarding the ROM on the affected side. At this time, with the midline of the body as the reference, the patient breathes in when moving closer to the midline and breathes out when moving away from the midline. The above movements are repeated 8 to 10 times and the physician examines whether the movement of the patient's head and neck area is normal. In case of a problem with the movement, the physician guides the patient by placing 1 hand on the posterior cervical region and the other hand on the face, thereby correcting the movement. After completing the repetitive movements, the maximum ROM is checked again and if it does not achieve normal ROM, the left-to-right turning motion is repeated. The procedure continues for a specified treatment time (within 15 minutes) and at the discretion of the physician, the treatment process could either be continued or undergo only the movement therapy or the acupuncture treatment without movement (additional acupoints if necessary) after the treatment process.

A total of 6 treatments will be performed 3 times a week for 2 weeks; however, depending on the patient's condition or circumstances, a total of 4 to 6 treatments for trapezius MSAT may be performed during 2 weeks.

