#### Active control group: acupuncture

2.3.2

The protocol for trapezius acupuncture is as follows; Acupuncture points are selected from primary meridians (SI15, TE15, and LI16 bilateral) and extraordinary meridians (GB20, BL10, SI14 bilateral, and GV14 unilateral) on the bilateral upper and middle trapezius according to the physician's discretion. Acupuncture is performed with needles inserted into 6 to 12 selected points. Disposable needles (30 mm ∗ 0.25 mm; Dong-bang Acupuncture, Korea) are used for the insertion, and depending on the characteristics of the acupuncture point, after the perpendicular or oblique insertion, a twirling method is performed for the patient to feel the acupuncture sensation.

A total of 6 treatments will be performed 3 times a week for 2 weeks; however, depending on the patient's condition or circumstances, a total of 4 to 6 treatments may be performed when conducting the treatment twice a week. Duration for the needle insertion will be approximately 15 minutes.

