##### Drug consumption

2.4.2.12

The type and dose of medication (medication prescribed due to current medical history or rescue medication) taken during the study period will be checked through a questionnaire during each visit. For treatments other than the medication taken such as the injections, the number of the treatments will be recorded.

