### Blinding

2.9

Due to the nature of the intervention in this study, it is impossible to blind the physicians and patients. However, in this study, the statistical analysis manager and the outcome assessor will be blinded to secure objectivity and reduce the bias as much as possible. Outcome assessment will be performed in a separate space before the treatment is performed by an assessor, who will not participate in the treatment and does not know the patient's group assignment, and has received standardized training for the data collection procedures.

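### The stated adverse-event method names no enquiry put alike to both arms, so unequal ascertainment in this open-label safety comparison cannot be excluded

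*Protocol article*

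**What the plan says.** Section 2.12 (Adverse events) sets a broad goal: "all adverse events occurring during the clinical trial will be examined and recorded". It then names the sources and the comparison: "Adverse events will be collected through patient complaints or observations, and the occurrence of adverse events between groups will be examined by occurrence frequency". Causality is also rated there: "The investigator will evaluate the causal relationship between the respective treatment method and the adverse events that occurred on a 6-point scale". No blinding is stated for that rating.

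The two treatments involve different contact with the physician:

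- **MSAT.** The Introduction says of the technique: "All movements are made under the observation and guidance of a physician". In section 2.3.1, "the physician rotates the neck alternately from left to right with 3 disposable needles" in the upper trapezius. The physician also looks for abnormal movement, corrects it by hand and re-checks range of motion, all within 15 minutes.
- **Control.** In section 2.3.2 the physician inserts needles at 6 to 12 points and twirls them. "Duration for the needle insertion will be approximately 15 minutes". The section describes no examination while the needles are in, and does not say whether anyone stays with the patient.

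Section 2.9 states that "it is impossible to blind the physicians and patients". It provides a blinded assessor for outcomes but does not give that person the collection of adverse events. A uniform instrument exists for medication: under section 2.4.2.12, drug use "will be checked through a questionnaire during each visit".

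**The concern.** Safety is one of the three aims in the Abstract and the Introduction, and the Introduction calls the existing safety evidence on MSAT insufficient. The planned safety result is a difference in event frequency between arms. Such a difference reflects harm only if an event has about the same chance of being recorded in either arm.

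One of the two named sources, observation, is supplied more generously by the MSAT procedure than by the control procedure as described. The other, complaint, depends on patients who know their treatment and, as far as section 2.12 says, are not all asked the same thing. The error could go either way. A physician moving and examining the neck may notice more, or may regard discomfort during movement as expected and record less. MSAT could then look more harmful than it is, or safer.

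**Working it through.** **1. The plan's own figure.** There is none to reproduce: section 2.12 gives no event rate, detection rate or test. The only usable design number is 64 patients per arm (section 2.6).

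**2. Where ascertainment is matched and where it is not.**

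| Route by which an event is noticed | MSAT | Control | Matched? |
|---|---|---|---|
| Number of sessions (2.3.1, 2.3.2) | 4 to 6 | 4 to 6 | Yes |
| Session length | within 15 min | about 15 min | About equal |
| Physical examination schedule (2.4.2.7) | same time points | same time points | Yes |
| Physician examination in session | built in and repeated | insertion and twirling only are described | Not shown to be |
| Standard adverse-event question | none named | none named | No instrument that would ensure it |

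The exposure is thus mainly to events noticed during a session. Events arising between sessions or in follow-up depend on complaint, which is open to reporting by unblinded patients but not to how closely a session is watched.

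**3. Sensitivity to unequal detection (every rate here is an assumption).** Let the true risk p be equal in both arms, with detection d_M in MSAT and d_C in control.

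Observed risk = p × d, so observed risk ratio = (p × d_M)/(p × d_C) = d_M/d_C. The ratio does not depend on p.

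With p = 0.20:

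- 80% against 50%: 0.16 against 0.10, ratio 1.60
- 70% against 60%: 0.14 against 0.12, ratio 1.17

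With p = 0.20, MSAT detection of 90% and 64 per arm (expected count = 64 × p × d), the last column is the probability that a two-sided Fisher exact test gives p < 0.05 although the true risks are equal:

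| Control detection | Ratio | Expected counts | Chance of false p < 0.05 |
|---|---|---|---|
| 90% | 1.0 | 11.5 v 11.5 | 2.9% |
| 75% | 1.2 | 11.5 v 9.6 | 4.5% |
| 60% | 1.5 | 11.5 v 7.7 | 10.5% |
| 45% | 2.0 | 11.5 v 5.8 | 23.5% |

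At 60% control detection, the last column runs from 4.4% to 17.1% as p goes from 10% to 30%. The Fisher test is for illustration only; the protocol states no test for adverse events.

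**4. Dilution.** These figures apply one detection rate to every event. Suppose only half of events occur in session and are detected at 90% against 60%, and the rest at 90% in both arms. Control detection is then 0.5 × 0.60 + 0.5 × 0.90 = 0.75 and the ratio is 0.90/0.75 = 1.2, not 1.5.

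**5. Direction.** If MSAT physicians discount events, so that detection is 60% in MSAT and 90% in control, the ratio is 0.60/0.90 = 0.67. The same mechanism then makes MSAT look safer.

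**The case against.** The strongest reply is that a condensed article has been over-read. Section 2.12 does not say that complaints must be unprompted, or that no other source is used. Section 2.10 refers to standard operating procedures and case-report-form guidelines, and the schedule in Table 1 is not visible here, so a visit-by-visit enquiry may exist. Control treatment is also hands-on, since twirling relies on the patient's response, and section 2.3.1 lets an MSAT session turn into acupuncture without movement. Sessions and physical examinations are matched, and outcomes are assessed before treatment by someone who does not know the group.

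Much of this stands. A reader might infer that events come only from volunteered reports, that control patients are left unwatched, or that the safety comparison is already biased. The article supports none of these. It does not limit its sources in those words, it is silent on who attends the control patient, and matched visits confine the exposure largely to in-session events. The ratios above only restate assumed detection rates.

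The reply does not remove the point. Section 2.12 is not silent on method: it names the sources and the comparison, and neither source is a common enquiry. Equal numbers of visits do not equalise what is noticed within a session, and the blinded assessor is not given this task.

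A further objection concerns the remedy. Resting the comparison only on answers to a question would leave out in-session events that the patient does not later report, and these are the procedural harms of most interest. That is correct, and the fix below keeps them.

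**Conclusion.** The point holds in a limited form. Followed as written, the plan compares event frequencies between open-label arms using one source that differs by design and another that is not standardised. Unequal ascertainment, mainly of in-session events, cannot be excluded. Its size and direction cannot be computed from the protocol: under the assumptions shown, the false ratio runs from 1.0 (equal detection) to 2.0, or below 1 if MSAT events are discounted. This is a cheap improvement to a stated method. It is neither a demonstrated bias nor a contradiction in the document, and it does not touch the primary outcome. It falls away if the full protocol or case report form already puts one common adverse-event question to both arms at every visit.

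**What to change.** 1. Add one identical, self-completed item for both arms to the questionnaire already used at each visit, including weeks 3 and 8. For example: have you had any new or worse symptom since the last visit? 
2. Have it completed before that day's treatment and, where pain scales are due, after them. Each session is then asked about at the next visit, and the pain scales are finished before an answer could hint at the arm.
3. In section 2.12, report the between-group frequency twice: for events elicited by this item, and for all recorded events. Show in-session observations and spontaneous complaints by source, and drop none of them from the comparison.

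The cost is one questionnaire item and one table, with no added staff. More minor events will be recorded in both arms. The answers still come from unblinded patients, so the item standardises the asking but does not remove reporting bias.

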### Data monitoring

2.13

Monitoring will be conducted to ensure the safety of the study's subjects and the integrity of the study data. Monitoring will be conducted through a total of 3 monitoring visits after the introductory meeting from the first subject screening time in the order of 2 regular monitoring visits, and 1 end-of-study monitoring visit at the end of the study. The monitoring will be conducted by the monitoring personnel in the host institution. Monitoring will be conducted by collating and comparing the case report forms and supporting documents, and examining the safety matters of the study's subjects.

Monitoring is planned to be conducted a total of 3 monitoring visits, 2 regular monitoring visits from the time of initial patient enrollment, and one end monitoring visit at the time of completion of the trial.

### Ethical consideration and dissemination

2.14

#### Ethical approval

2.14.1

Before initiating the study, the study protocol, CRF, informed consent form, and patient recruitment announcement will be submitted to the IRB at each site to obtain the appropriate approval for the study (JASENG 2020–07–014, JASENG 2020-07-015, JASENG 2020-07-016, and JASENG 2020-07-017). All modifications to the protocol, CRF, informed consent form, and others will be subject to the approval of the IRB. All modifications will be updated on the trial registry. All clinical investigators participating in this study will be educated about the Helsinki Declaration and the Korean Good Clinical Practice Guidelines, the study protocol, and the SOP to protect the patients participating in this study.

#### Patient consent

2.14.2

Before the start of the clinical study, the investigator will provide sufficient information on the overall processes of clinical trial and treatment in a face-to-face meeting with the patient. The Investigator will obtain a signed informed consent from the patient and provide a copy of the consent form to the patient.

#### Dissemination

2.14.3

The results of this study will be shared with the participants, healthcare professionals, and the public by publishing or through trial registry. Only investigators who were directly or indirectly involved in the study will be listed as authors on study-related publications. The datasets used in the study are available from the corresponding author on reasonable request.

### Confidentiality

2.15

All personal information data of study subjects participating in this study will be managed under the strict supervision of the IRB and the personal information of the study subjects will be kept strictly confidential. All data collected from the subjects, that provided their consent to participate in this study, will be treated anonymously. In case of sharing this information with other institutions for research purposes, they may be provided in the form of arbitrary codes after excluding personal information.

### Ancillary and post-trial care

2.16

In the case of direct harm in relation with this study, appropriate medical care may be obtained as determined by the investigator. Compensations for any damage would be proceeded according to the pre-designated insurance policy related to the study. All participants will be provided with an emergency contact number to reach study investigators so that they can receive the necessary support when they have any question or problem.

## Discussion

3

For spinal disease, the treatment that utilizes passive and active movements of the patient after needle insertion has gained recent widespread usage in China as well as in Korea.^[13,14]^ Liu et al^[28]^ and Lin et al^[29]^ reported greater improvements in pain and ROM in the MSAT group compared to the control group with other types of treatments such as loxoprofen, physical therapy, and conventional acupuncture in RCT for acute low back pain patients. Shin et al^[30]^ reported greater effective improvement of pain and physical functionality in the MSAT treatment group compared to the diclofenac injection group in their study with patients with severe, acute low back pain. Luo et al^[31]^ reported superior outcomes in the MSAT group compared to the conventional acupuncture treatment group in a short-term treatment in their clinical study on cervical spondylosis. In an RCT with 100 WAD patients from traffic accidents conducted by Kim et al,^[15]^ the group that underwent a combination of trapezius MSAT and integrative Korean medicine treatment demonstrated a faster pain reduction and ROM improvements than the group with integrative Korean medicine treatment alone. However, qualitative evidence for the effectiveness and safety of MSAT is still insufficient.

To our knowledge, this study is the first well-designed, multi-centered RCT that evaluates the effectiveness, safety, and cost-effectiveness of MSAT for acute neck pain. Due to the nature of the study design, the physician and patients cannot be blinded, but the outcome assessors and statistical analysts will be blinded to retain objectivity as much as possible.

The results of this study will be useful for clinicians in primary medical institutions, that are frequently visited by patients with acute neck pain, and for policymakers working in healthcare insurance.
